The modern concept of empowerment is increasingly defined as strengthening the capabilities and the self-reliance of individuals [38]. We use Aubel’s definition, who describes empowerment as ‘the ability of individuals or groups to improve capacities, to critically analyse situations and to take actions to improve those situations’ [39]. This definition applies bottom-up thinking to drive behaviour change [40–42], requiring an environment in which pregnant women can engage in open communication [40]. The process of empowering pregnant women is expected to improve their health, as they are supported to make healthier choices, for example in terms of nutrition [6, 21]. This can therefore result in improved child health and providing children with a healthy and successful start of life [2, 3].

P4HP has been developed in the past years together with stakeholders, aiming to empower pregnant women to have a healthier diet quality [42–45]. This intervention may contribute to enduring new-borns with a healthy, successful start of life [2, 3] and has the potential to improve health across generations. P4HP uses a women-centered empowerment approach, to prioritize the woman’s individual needs, as defined by the woman herself, assigning to the woman’s choice, control, and continuity of care. P4HP allows women to be empowered, gaining control over their lives and learning how to achieve goals that are meaningful to them. Individuals are most likely to change their behaviour to make healthier choices when they are educated and motivated to do so, in addition to environments and policies supporting these decisions [46].

A similar intervention in which empowerment and diet quality among pregnant women is central has not been implemented before to our best knowledge. The research will contribute to theoretical development by providing practice-based evidence [47, 48]. This mixed methods study aims to 1) evaluate the effectiveness of P4HP regarding diet quality, empowerment, Sense of Coherence (SOC), Quality of Life (QoL), and Self-Rated Health (SRH) using a cluster randomized controlled trial (C-RCT), and 2) evaluate P4HP in terms of multidisciplinary collaboration, facilitators and barriers using a process evaluation. This way, as we retrieve both information about what is needed to achieve an effect and about what is needed in the implementation and in the multisectoral collaboration, we gain insight in both the effectiveness as well as the feasibility of P4HP.

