### Data analyses

#### Quantitative analyses C-RCT

Statistical analyses will be carried out using IBM SPSS Version 25 (Statistical Package for Social Sciences). Data cleaning will be performed before the final review to check for missing data or outliers. We expect data missing will be at random, and if so, all available data from T0 and T1 will be used to conduct the analyses.

All data will be quantitatively presented in tables (Tables 2 and 3). BMI, the DHD2015-index, PRES score, SoC-3 score, QoL VAS score, and GSRH-score will be presented as ordinal data. Ethnicity, education, and living situation will be presented as nominal data. All data will be entered and verified, and scores will be calculated for multiple-item instruments (i.e. DHD2015-index, PRES, SoC-3). Descriptive statistics will be performed to tabulate mean (or median) values of all study characteristics and baseline values of the independent variables. Chi-square (for categorical variables) and Student’s t-tests (for continuous variables) will be used to compare the descriptive statistics between study groups and to identify potential covariates. The number of participants, as well as means (standard deviations, SDs), median or % (numbers of patients), will be tabulated where appropriate.

**Table 2 Tab2:** Baseline characteristics for intervention and control group

	Intervention group (P4HP)	Control group (standard birth care)	Difference in means (95% CI)	*P*-value
	**Mean (SD)**	**Mean (SD**		
*Age*				
	**% (n)**	**% (n)**		
*Ethnicity (% native Dutch)*				
*Education (low, medium, high)*				
*Living situation (alone, with a partner, with children, with partner and children)*				
	**Mean (SD)**	**Mean (SD)**		
*BMI* *Diet quality (DHD2015-index)*				
*Empowerment (PRES)*				
*Sense of Coherence (SOC-3)*				
*Quality of Life (QoL VAS)*				
*Self-Rated Health (GSRH)*

**Table 3 Tab3:** Baseline, post-intervention, and change scores for intervention and control group

	T0 *(M, SD)*	T1 *(M, SD)*	Change T1 *(change ± SE)*	Effect estimate *(95% CI)*	Group differences *(P-value)*
BMI *(kg/m2)* Intervention (n=) Control (n=) Effect size					
Diet quality *(DHD2015-index)* Intervention (n=) Control (n=) Effect size					
Empowerment *(PRES)* Intervention (n=) Control (n=) Effect size					
Sense of Coherence *(SOC-3)* Intervention (n=) Control (n=) Effect size					
Quality of Life *(QoL VAS)* Intervention (n=) Control (n=) Effect size					

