Self-Rated Health *(GSRH)* Intervention (n=) Control (n=) Effect size					

Linear mixed models will be used to analyse the data. Using linear mixed models allows for the analysis of different sources of variation in data and for unequal variances and correlations. This flexible method is suitable for analysis of the clustered data as it allows to calculate the treatment effect. When there are multiple levels, such as pregnant women seen by the same midwifery practice, the variability in the outcome can be thought of as either within-group or between-group. Pregnant women-level observations are not independent, as within a midwifery practice pregnant women and their guidance are more similar. Units samples at the highest level (in our research, midwifery practices) are regarded as independent. With this method also confounders can be taken into account [102]. After performing the linear mixed models analysis, the final results will be presented in Table 3. This table will display means and standard errors, the between-group differences, and the *p*-values for the treatment effect for all primary and secondary outcomes.

All primary and secondary outcomes will be tested via linear mixed models. Other subgroup analyses include age, ethnicity, individual or group (CenteringPregnancy) consultation, educational level, living situation, working situation, and income level. These variables will be checked if they differ across the groups using an independent Student’s t-test when continuous and normally distributed. If skewed, a Wilcoxon signed-rank test will be done. Variables that are not continuous, will be checked for differences between groups using a chi-square test. Two-sided *p* values < 0.05 will be regarded as statistically significant.

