## Discussion

This paper describes the study protocol for a mixed methods study consisting of a C-RCT with an intervention group and a control group and a process evaluation. The study protocol includes the evaluation of P4HP, an empowerment intervention to improve diet quality among pregnant women. To our knowledge, this is the first C-RCT that evaluates the effectiveness of an empowerment intervention to improve diet quality in The Netherlands. Research in this field is needed because there is limited evidence of effective empowerment interventions regarding diet quality during pregnancy. To ensure that P4HP fits into standard birth care, various stakeholders have been involved in all steps of the development process. Our study will provide important and unique information on how to empower pregnant women to achieve improved diet quality by midwives and dieticians. Having both a quantitative and qualitative evaluation of P4HP will create a comprehensive overview of both the impact of P4HP and how best to implement it more broadly in practice.

P4HP will be assessed on diet quality, empowerment, SOC, QoL, and SRH. Although these assessments were selected intentionally based on previous research, the intervention may still produce an effect that is not directly assessed by our quantitative assessments. The process evaluation is therefore added to capture these indirect effects using semi-structured interviews. Innovative is that outcome measures include empowerment and SOC, something not common in C-RCT studies. Previous studies found evidence that SOC significantly changed and that those with a weaker SOC were more likely to have a stronger SOC after the intervention that included experimental learning [86, 104], as these groups have most to gain. In case we find change in SOC, it indicates that participants of P4HP benefit from the intervention; providing a more complete picture of the interventions’ successes. Two limiting factors of using Eetscore to assess diet quality are that it is only available in Dutch and oriented to a Dutch dietary pattern. Consequently, this unfortunately limits women who do not speak Dutch and with other diet patterns from participating.

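### No outcome is named as primary: six outcomes, BMI among them, are each tested at 0.05 with no hierarchy, and the sample-size effect of 0.4 is tied to none of them

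*Protocol article*

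**What the plan says.** Under Quantitative analyses C-RCT, the article states that "All primary and secondary outcomes will be tested via linear mixed models" and that Table 3 will show p-values "for the treatment effect for all primary and secondary outcomes". The same section gives a single criterion: "Two-sided *p* values < 0.05 will be regarded as statistically significant".

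The text never assigns an outcome to the primary or the secondary class. The aims at the end of the Background are to "evaluate the effectiveness of P4HP regarding diet quality, empowerment, Sense of Coherence (SOC), Quality of Life (QoL), and Self-Rated Health (SRH"), which is five outcomes side by side. The Discussion repeats the five: "P4HP will be assessed on diet quality, empowerment, SOC, QoL, and SRH".

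Table 3 ("Baseline, post-intervention, and change scores for intervention and control group") has six rows: BMI, diet quality, PRES, SOC-3, QoL VAS and GSRH. Each has columns for an effect estimate and a p-value. The BMI row has the same layout as the rest: "BMI *(kg/m2)* Intervention (n=) Control (n=) Effect size".

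Sample size estimation gives an effect size of 0.4, 80% power, alpha 0.05 and an ICC of 0.02, leading to 7 clusters of 25 women per arm. It does not say which outcome the 0.4 refers to.

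**The concern.** The article uses the labels primary and secondary and builds its results table on them, but the labels point to nothing. A reader cannot tell which hypothesis the 5% error and 80% power were meant for.

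Nor can the lead outcome be inferred with certainty. The aims put diet quality first. The Non-blinded C-RCT section puts empowerment first. The stated purpose of P4HP, empowering women towards a healthier diet, fits either.

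Without a named primary outcome, the emphasis can be chosen after the results are known. The Discussion already leans this way: it would take a change in SOC, taken alone, as a sign that participants benefit. The abstract makes national implementation depend on P4HP being proven effective, and no passage defines that.

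BMI adds an inconsistency. It is tested in Table 3 but is not in the aims. T1 follows completion of P4HP, whose last session is at about 32 weeks, so BMI change will include gestational weight gain. The article does not say which direction of difference would favour P4HP.

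**Working it through.** **Inputs**
- Outcomes with a treatment p-value: 6 (Table 3), or 5 without BMI (aims and Discussion).
- Threshold: two-sided 0.05 for each test (Quantitative analyses C-RCT).
- Effect size 0.4, power 80%, alpha 0.05, ICC 0.02, 7 clusters of 25 per arm (Sample size estimation).
- Correlation between outcomes: not given in the article, so assumed, and a range is shown.

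**Step 1: the plan's own figure**
- Design effect = 1 + (25 − 1) × 0.02 = 1.48.
- Clusters per arm, using t on 2 × (7 − 1) = 12 df: 2 × 1.48 × (2.179 + 0.873)² / (25 × 0.4²) = 6.89, so 7.
- Noncentral-t power at 7 clusters per arm is 80.6%.

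The stated size is reproduced, and it holds for one outcome tested at 0.05. The calculation is sound; what is missing is the outcome it belongs to.

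**Step 2: at least one false significant result, either direction, no true effect on any outcome**

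For m independent tests the chance is 1 − 0.95^m:
- m = 5: 1 − 0.95⁵ = 22.6%
- m = 6: 1 − 0.95⁶ = 26.5%

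For correlated outcomes, the figures come from simulating 1,000,000 sets of normal test statistics with a common pairwise correlation and counting sets with any |z| > 1.96.

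| Assumed correlation | 5 outcomes | 6 outcomes |
|---|---|---|
| 0 (formula) | 22.6% | 26.5% |
| 0.3 | 20.9% | 24.2% |
| 0.5 | 18.3% | 20.8% |
| 0.7 | 14.9% | 16.4% |

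**Step 3: the favourable direction only**

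Each two-sided 0.05 test leaves 0.025 in the favourable tail.
- Six independent tests: 1 − 0.975⁶ = 14.1%. At correlation 0.5: 10.4%.
- Five independent tests: 1 − 0.975⁵ = 11.9%. At correlation 0.5: 9.2%.

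The comparison value for a single test is 2.5%. The six-outcome figures assume that BMI has a favourable direction, which the article does not state.

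**Step 4: what the choice of primary does to power**

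One primary outcome at 0.05 keeps the 80.6%. If alpha were instead split by Bonferroni at the same size (d = 0.4, ICC 0.02, 12 df), power per outcome would be about:
- 69% for two co-primary outcomes (0.025 each)
- 53% for five outcomes (0.01 each)
- 50% for six outcomes (0.0083 each)

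The sample size therefore supports one primary outcome at the stated power, and no more than one.

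**The case against.** Diet quality is strongly implied as the lead outcome. It comes first in the aims, and the Discussion describes the trial as testing an empowerment intervention meant to improve it. The trial was also prospectively registered. The registry record, the SPIRIT diagram and the additional file are not shown and may name a primary outcome. Multiplicity rules for secondary outcomes are often left to an analysis plan. All of this is fair, and it is why the fix should follow the registration. It does not repair the article, which uses the labels without assigning them and gives a sample size without an outcome.

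Three stronger readings are tempting, and the text does not support them.
- **That the chance of falsely claiming effectiveness is one in four or five.** That figure counts false results in both directions, and a significant difference favouring control is not a claim of benefit. For benefit alone the figure is about 10–14%.
- **That any one significant outcome establishes effectiveness.** No passage says so. The closing part of the Discussion speaks of improvement in diet quality, empowerment and other outcomes together, and the SOC remark goes on to present SOC as completing the picture.
- **That the seven variables listed as subgroup analyses add further effect tests.** The section calls them subgroup analyses, but then describes checking whether they differ between groups by t-test, Wilcoxon or chi-square test. Those are comparability checks, so they are not counted here.

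Keeping BMI is also defensible, since the Background links poor diet to excessive gestational weight gain. The objection to it is its undefined status.

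**Conclusion.** The point stands in this form: the labels are unassigned, the effect size of 0.4 is not linked to an outcome, and six outcomes are tested at an unadjusted 0.05 with no rule for weighing them. BMI is one of the six without being in the aims.

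With no true effect on any outcome, the chance of at least one false significant result in either direction is 26.5% under independence and 20.8–24.2% at correlations of 0.5 to 0.3. It falls below one in five above a correlation of about 0.6. In the favourable direction only it is 10.4–14.1% for correlations from 0.5 to 0. These figures rest on assumed equal correlations and on normal test statistics.

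This is more than missing detail. The choice of primary outcome carries weight only if it is made before outcome data are seen, and the sample size gives about 80% power for one outcome only.

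**What to change.** - Name one primary outcome that agrees with the registration. The total diet-quality score (DHD2015-index, 0–160) at T1 fits the stated aim. If the registration names something else, the article should follow it or explain the difference.
- In Sample size estimation, state that the effect size of 0.4, the 80% power and the alpha of 0.05 refer to that outcome.
- Label the other outcomes as secondary. Test them with Holm or in a fixed order, or report estimates with 95% confidence intervals and make no significance claim.
- Give BMI a status: descriptive, secondary, or out of the effect rows of Table 3.

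The cost is a few sentences and possibly one table row. The sample size stays at 7 clusters of 25 per arm. The price is that secondary outcomes, including empowerment and SOC, lose stand-alone confirmatory status, and the Discussion's remark on SOC would need wording to match.

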#### Sociodemographic data

Questions to collect name, year of birth, phone number, email, postal code digits, living situation, ethnicity, educational level, and personal and household income.

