### Intervention

P4HP is a non-invasive empowerment intervention and consists of four extra moments for pregnant women to discuss nutrition with their midwife and a dietician. P4HP distinguishes itself from standard birth care by its empowering approach towards improving diet quality during pregnancy. The intervention is free of charge for the women and takes place in an individual or group setting (via CenteringPregnancy). P4HP is designed to be flexible, meaning that the professional has the freedom to adapt to what the individual or group needs at each session. This research is in line with current Dutch policy regarding empowerment, dietary guidelines, and prevention [96–99].

Table 1 provides an overview of the P4HP-elements. For each element of the intervention, it explains the goal(s), the activity, the estimated time that is needed for the activity, and the tools as well as who guides the activity. The exact time investment per session topic will be discussed with and adapted to the possibilities of the midwives and dieticians.

**Table 1 Tab1:** Overview of the P4HP-intervention

Session	Time	Goal(s)	Activities	Tool

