Materials and language used in P4HP are designed to be suitable for low SES pregnant women – the group who will mostly benefit from this intervention because of a general sub-optimal adherence to dietary guidelines [8–10]. We assume P4HP thus aligns with women of all SES groups. As it is not ethical to discriminate the inclusion of participants on their SES-status, all SES-groups visiting participating midwifery practices will be included in this study. In the results we will report on differences in outcomes between SES groups.

This study will make a significant and to our knowledge unique scientific and socially relevant contribution about using an empowerment intervention to improve the diet quality of pregnant women in the Netherlands. If P4HP improves pregnant women’s diet quality, empowerment and other health-related outcomes, the impact may have health, social, and economic benefits. We anticipate that the study outcomes have the potential to change the way nutrition is addressed during pregnancy. The findings will directly benefit pregnant women and their children, as well as inform academics and others who strive to produce interventions that can be effectively implemented in routine care using multisectoral collaboration. If P4HP proves to be an effective and feasible intervention, further research will be done on the extension towards the preconception and postpartum phase.

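### The tests attached to the subgroup list are balance checks, so no stated method assesses whether the effect of P4HP differs by subgroup; one listed variable, working situation, has no listed data source

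*Protocol article*

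**What the plan says.** Under Quantitative analyses C-RCT, after stating that all outcomes are tested by linear mixed models, the protocol article continues: "Other subgroup analyses include age, ethnicity, individual or group (CenteringPregnancy) consultation, educational level, living situation, working situation, and income level". Three sentences on method follow. The first reads: "These variables will be checked if they differ across the groups using an independent Student’s t-test when continuous and normally distributed". The second names the signed-rank version of the Wilcoxon test for skewed variables, and the third gives a chi-square comparison for the categorical ones.

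Earlier in the same section, t-tests and chi-square tests are already planned to compare characteristics between the study groups and to find potential covariates.

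The Sociodemographic data section itemises what is asked: name, year of birth, contact items, postal code digits, and "living situation, ethnicity, educational level, and personal and household income". The Intervention section says that P4HP "takes place in an individual or group setting (via CenteringPregnancy"). The Control section does not mention format. The Discussion describes low-SES women as the group expected to gain most, and adds: "In the results we will report on differences in outcomes between SES groups".

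**The concern.** A subgroup analysis asks whether the treatment effect differs between kinds of women. The tests written under that label ask whether the arms contain different kinds of women. An analyst who follows the paragraph as printed produces a second baseline table and nothing on effect modification.

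The SES sentence in the Discussion does not fill the gap. The Background says that adherence to dietary guidelines is poorer at lower SES. A difference in diet quality between SES groups is therefore expected even if P4HP helps everyone equally, or helps no one. Such a difference could be misread as evidence on who benefits.

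Two of the seven variables raise further problems. Working situation has no question behind it in the data collection list. Individual versus group consultation is described only as a way of delivering P4HP, so it may have no counterpart in the control arm.

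**Working it through.** **1. What each stated analysis can show.** For an outcome Y, arm A (0/1) and a binary SES indicator S, write

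E[Y] = b0 + b1·A + b2·S + b3·A·S.

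Effect modification is b3.

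- *The three test sentences* compare the distribution of S between A = 1 and A = 0. Y does not enter, so none of b0 to b3 is estimated. None of the three sentences involves an outcome or a treatment effect.
- *The SES sentence, read literally*, compares Y between S = 1 and S = 0. With 1:1 allocation and S balanced across arms, this equals b2 + b3/2. If b3 = 0, it equals b2, the SES main effect, which the Background leads one to expect is not zero.

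The section does not define *groups* in the test sentences. The earlier balance comparison uses the same t-test and chi-square between study groups, so the arms are the natural reading.

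**2. Variables against data sources.**

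| Listed for subgroup analysis | Source in the article |
|---|---|
| Age | Year of birth |
| Ethnicity, education, living situation, income | Sociodemographic data |
| Individual or group consultation | Intervention section only, as delivery format |
| Working situation | None in Sociodemographic data, the other assessment sections or Table 2 |

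Five of the seven have a listed question, one is a delivery feature, and one has no source.

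**3. Plan's own figure.** Inputs from Sample size estimation: effect 0.4, ICC 0.02, 25 women per practice, 7 practices per arm, alpha 0.05, power 80%.

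- Design effect = 1 + (25 − 1)·0.02 = 1.48.
- Clusters per arm, t distribution on 2·(7 − 1) = 12 df: (t0.975 + t0.80)²·2·1.48/(25·0.4²) = 6.89, so 7.
- Power at 7 per arm is 80.6% by the noncentral t.

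The stated sample size reproduces and is not in question.

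**4. What an interaction test could deliver.** Assumptions that the article does not give: total SD 1, a binary modifier varying within practices with prevalence p, no loss, no gain from baseline adjustment, and a normal approximation. With 175 women per arm:

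SE = √[(1 − 0.02)·(2/175)·(1/p + 1/(1 − p))]; power for 0.4 SD = Φ(0.4/SE − 1.96); detectable at 80% power = (1.96 + 0.84)·SE.

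| Split | SE | Power for 0.4 SD | Detectable at 80% power |
|---|---|---|---|
| 50/50 | 0.212 | 47% | 0.59 SD |
| 30/70 | 0.231 | 41% | 0.65 SD |
| 20/80 | 0.265 | 33% | 0.74 SD |

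An interaction as large as the whole effect that the trial is powered for would be missed at least half the time.

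**5. Side observation on the same sentences.** The signed-rank test is for paired data, but here it stands in for an independent-samples test. None of the three tests takes account of clustering by practice.

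**The case against.** The strongest reply is that a journal article condenses the plan and that an interaction model is the sort of detail left to a statistical analysis plan, which is not at hand. The three sentences may be a balance check that landed after the wrong sentence. The SES sentence closes a paragraph about who gains from P4HP and may mean SES-specific effects. The remark that low-SES women benefit most explains how the materials were designed; the stated aims contain no hypothesis of effect modification.

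Much of this stands. A reader might infer that effect modification will never be examined. The article does not support that: it announces subgroup analyses, the SES sentence is ambiguous, and a fuller document could hold the model. A reader might also multiply seven variables by the outcomes and predict false-positive subgroup findings. That does not follow either. The article does not say which outcomes the subgroup analyses cover, and the tests as written involve no outcome at all.

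What does not stand is that this is only missing detail. The article states a procedure under the subgroup label, and that procedure does not answer a subgroup question. If an unseen plan specifies an interaction, it departs from this text and the two must be reconciled. The full questionnaire could contain a work item, but the printed list is itemised and lacks one. The consultation-format point is a query, because it depends on what control practices record. A descriptive comparison within the intervention arm would be legitimate if labelled so.

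**Conclusion.** The point holds in a limited form. The tests stated for the seven subgroup variables are a balance check and cannot show whether the effect of P4HP differs by subgroup. The SES commitment has no method and, read literally, describes a main effect. Working situation is listed for analysis but not for collection.

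This should be corrected, but it touches neither the main treatment comparison nor the sample size. It rests on reading *groups* as the study arms, which the earlier balance comparison supports but the sentence does not spell out. The power figures (47% at 50/50, 33% at 20/80, for 0.4 SD) describe the recommended interaction test under assumed splits. They are not an error in the plan; they are the reason to keep subgroup results exploratory.

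**What to change.** 1. Keep one description of baseline characteristics by arm and remove the three test sentences from the subgroup paragraph. This also removes the misplaced signed-rank test.
2. State the subgroup method, for example: *Effect modification will be assessed by an arm-by-subgroup interaction in the linear mixed model with practice as cluster. The first subgroup variable is [education or income, chosen by the sponsor in advance] as the marker of SES. The remaining variables are exploratory and will be reported as estimates with 95% confidence intervals.*
3. Tie the SES sentence in the Discussion to that interaction, so that a difference in outcome level between SES groups is not presented as a difference in benefit.
4. Add working situation to the T0 questionnaire or delete it from the list.
5. For individual versus group consultation, either record in both arms whether the practice offers CenteringPregnancy, or label the comparison as descriptive within the intervention arm. The first option asks about the practice and not about the format a woman received, so the sponsor should choose knowingly.

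The cost is wording, plus one T0 question and one practice-level field if those options are taken. The question is best added before T0 collection starts, since women already enrolled would lack it. The sample size does not change. The remaining limitation is the low interaction power, which the report should state.

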#### Diet quality

We derive scores for diet quality using Eetscore [77]. Eetscore is a validated web-based screening tool to determine the diet quality of Dutch adults and suitable for assessing change in diet quality over time. Eetscore consists of a short food frequency questionnaire in an accessible writing style that is scored with the Dutch Healthy Diet index 2015 (DHD2015-index) to assess adherence to the Dutch food based dietary guidelines of 2015 of the Dutch health Council [73]. The DHD2015-index has been validated with 24 h dietary recall and FFQ data. In addition, to the DHD2015-index, a 16th component for unhealthy choices has been added. The questionnaire to determine this diet quality score consists of 40 questions with sub-questions inquiring about the consumption of 54 foods or food groups. Based on the answers a total score and 16 sub scores will be calculated. Sub scores of Eetscore are available for 1) vegetables, 2) fruit, 3) whole grain products, 4) legumes, 5) nuts, 6) dairy, 7) fish, 8) tea, 9) fats and oils, 10) coffee, 11) red meat, 12) processed meat, 13) sugar-containing beverages, 14) alcohol, 15) sodium and 16) unhealthy choices. Each component will be scored on a scale ranging from 0 (non-adherence) to 10 (complete adherence), providing a total score between 0 and 160. For the calculation of the scores, specific cut-off and threshold values are used. Since Eetscore is developed for the general Dutch adult population, it has been adapted to fit the requirements of pregnant women. The (sub)scores were adapted based on the dietary recommendations for pregnant women provided by the Dutch Health Council and the Netherlands Nutrition Centre [78]. We use the web-based version of Eetscore which can be filled out in about 10-15 min.

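### A paired test (Wilcoxon signed-rank) is named for skewed background variables in two unpaired arms, and four continuous scores are labelled ordinal against the plan's own tables and model

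*Protocol article*

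**What the plan says.** All of this stands in the protocol article under Quantitative analyses C-RCT.

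**Test for background variables.** The section lists them: "Other subgroup analyses include age, ethnicity, individual or group (CenteringPregnancy) consultation, educational level, living situation, working situation, and income level". It continues: "These variables will be checked if they differ across the groups using an independent Student’s t-test when continuous and normally distributed". For the other cases it gives two rules: "If skewed, a Wilcoxon signed-rank test will be done", and "Variables that are not continuous, will be checked for differences between groups using a chi-square test".

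**Measurement level.** Earlier in the section: "BMI, the DHD2015-index, PRES score, SoC-3 score, QoL VAS score, and GSRH-score will be presented as ordinal data". Ethnicity, education and living situation are called nominal. Table 2 nevertheless reports all six scores as mean (SD), with a column for the difference in means and its confidence interval. Table 3 reports all six as mean and SD at T0 and T1, a change with standard error, and an effect estimate.

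**Baseline comparison.** "Chi-square (for categorical variables) and Student’s t-tests (for continuous variables) will be used to compare the descriptive statistics between study groups". The stated purpose includes finding possible covariates. No test is named for ordinal variables.

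**Outcomes.** "All primary and secondary outcomes will be tested via linear mixed models".

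**The concern.** Two statements are wrong or contradictory as written.

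First, the signed-rank test works on within-pair differences. Women are allocated by practice, and the protocol describes no matching of practices or of women. The test named for skewed data is therefore not the counterpart of the independent t-test named one sentence earlier.

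Second, BMI, the diet score, PRES and the QoL VAS cannot be ordinal in the label and also be summarised by means, SDs and differences in means and fitted with a linear model. Someone programming Table 2 would have two conflicting instructions, and no named test if the label is taken literally.

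What is at stake is modest: the between-arm checks on background variables, and through them possibly the choice of confounders for the mixed model.

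**Working it through.** The plan gives no figure on this point, so there is none to reproduce. The check compares passages and adds one illustration.

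**Is there any pairing?**
- Between arms: no. Allocation is by practice, 7 against 7 (Non-blinded C-RCT; Sample size estimation), by an Excel scheme with no matching described (Cluster and participant recruitment).
- Within a woman, T0 to T1: not for the sociodemographic variables in the list. Data collection and assessments says the T1 questionnaires leave out sociodemographic data, so age and income have no second value to pair with.
- The neighbouring test is the independent t-test. A two-sample comparison is clearly meant.

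**What the two statistics use.** Let X and Y be the values in the two arms.
- Signed-rank: form D_i = X_i − Y_i for each pair, rank |D_i|, and sum the ranks where D_i > 0. Reordering one arm changes every D_i.
- Rank-sum (Mann-Whitney): count how often X_i exceeds Y_j over all i and j. Row order does not matter. With 7 × 25 = 175 women per arm, this uses 175 × 175 = 30,625 comparisons; the signed-rank test uses 175 differences.

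**Illustration.** Assumptions, none from the protocol: standard lognormal data, a shift added to one arm, no clustering, two-sided 0.05, 3,000 runs per row.

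| Setting | Rank-sum rejects | Signed-rank, arbitrary pairs, rejects |
|---|---|---|
| 175 v 175, no difference | 5.3% | 5.1% |
| 175 v 175, shift 0.3 | 91.4% | 66.0% |
| 170 v 150, shift 0.3 | 88.9% | 60.6% (after discarding 20 women) |

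In one simulated data set (175 v 175, shift 0.25) the rank-sum p was 0.004. Over 2,000 random pairings of the same data, the signed-rank p ran from 0.009 to 0.41, with median 0.10. With 170 v 150 and no discarding, the procedure stops with an error. Exactly equal arms cannot be relied on, because recruitment may close on 31-12-2022 before every practice has 25 women.

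**Which variables does the rule reach?** Ethnicity, consultation format, education, living situation and working situation are categorical. Age is continuous, and Table 2 already plans it as mean (SD). Income may be continuous or banded; the article does not say. That leaves at most two variables.

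**Label against use.**

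| Score | Scale in the protocol | Label | Use in tables and model |
|---|---|---|---|
| BMI | kg/m2 | ordinal | mean (SD) |
| DHD2015-index | "providing a total score between 0 and 160" | ordinal | mean (SD), linear mixed model |
| PRES | score from 16 questions | ordinal | mean (SD), linear mixed model |
| QoL VAS | 0 to 100 on a 100 mm line | ordinal | mean (SD), linear mixed model |
| SoC-3 | sum of three items scored 1 to 3, so 3 to 9 | ordinal | mean (SD), linear mixed model |
| GSRH | five ordered categories | ordinal | mean (SD), linear mixed model |

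The label does not fit the planned use for the first four. It is right for GSRH and defensible for SoC-3.

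**The case against.** The strongest reply is that these are two wording slips with little reach, and much of it stands. The signed-rank sentence follows directly on the list of background variables, and no outcome score is on that list. The sentence about identifying covariates names chi-square and t-tests, not a Wilcoxon test, so the route from this slip to the adjusted model is possible but not stated. Type I error stayed near 5% under arbitrary pairing, so the slip does not produce false positives. With unequal arms the procedure would fail before giving a p-value, and the error would probably be noticed.

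A reader might infer more:

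- *That the ordinal label sends the diet score and the other scales to chi-square as non-continuous variables.* The documents do not support this. The label concerns presentation, the chi-square rule belongs to the listed background variables, and Table 2 gives these scores a difference in means, which points to a t-test.
- *That every row of Table 3 gets a wrong p-value.* Table 3 is filled from the linear mixed models. Neither the signed-rank nor the chi-square rule feeds it.
- *That the three SOC groups enter a linear model.* The tables and the label refer to the SoC-3 score; the groups are an additional classification.
- *That linear models for GSRH and SoC-3 are an error needing cumulative-logit models.* A linear model for a short ordered score is a common choice. The alternative is optional and could be left to an analysis plan.

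The reply does not remove the two slips. Both are positive statements in the text, not detail that an article leaves out.

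**Conclusion.** The point holds in limited form. The signed-rank test is the wrong test for two independent arms; this rests on the design and on the adjacent independent t-test, not on any assumption. It reaches at most age and possibly income. The harm is a result that depends on row order, lost power (66% against 91% under the illustrative assumptions above) and a test that cannot be run on unequal arms without discarding women. The simulated figures would change with the distribution and the shift; the dependence on row order would not go away.

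The ordinal label is a separate inconsistency for BMI, the DHD2015-index, PRES and the QoL VAS. It needs correcting because the tables and model treat them as continuous. Neither issue is shown to alter a treatment-effect estimate or an outcome p-value. The correction is small, but should be made.

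**What to change.** 1. Replace the signed-rank test with the Wilcoxon rank-sum (Mann-Whitney) test for skewed continuous background variables. Alternatively, drop the test and describe the arms. Dropping is cleaner, because the section itself says that women within a practice are not independent and the rank-sum test also ignores this.
2. State that BMI, the DHD2015-index, PRES and the QoL VAS are treated as continuous, in line with Tables 2 and 3 and the linear mixed models. Keep ordinal for GSRH and, if wished, SoC-3.

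The cost is two or three sentences. No new data, additional model or change to the sample size is needed.
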